### Study objectives

The Parent Study and Extension Phase enable the investigation of both the symptomatic (12-week) and long-term (1-year) safety and efficacy of treatment with N-acetyl-L-leucine. The primary objective of the Parent Study is to evaluate the efficacy of N-acetyl-L-leucine versus placebo based on the Scale for the Assessment and Rating of Ataxia (SARA) or modified SARA (mSARA). In the Extension Phase, the primary objective is to evaluate the effects of N-acetyl-L-leucine based on the modified (5-domain) Niemann-Pick disease type C Clinical Severity Scale (NPC-CSS).

For both study phases, the secondary objectives are:To assess the clinical efficacy (symptomatic and long-term) of N-acetyl-L-Leucine on symptoms of ataxia, functioning, and quality of life for patients with NPCTo evaluate the safety and tolerability of N-acetyl-L-leucine at 4 g/day in patients with NPC aged ≥ 4 years and olderExtension Phase only: characterize the pharmacokinetics of N-acetyl-L-leucine in NPC patients

### Safety and efficacy parameters

#### Primary efficacy endpoint

The original SARA scale is an eight-item clinical rating scale (range 0–40, where 0 is the best neurological status and 40 is the worst). It is a reliable and valid clinical scale with a high internal consistency that measures the severity of symptoms and ataxia and increases with disease stage [16].

The original unmodified SARA was selected as the primary endpoint based on advice from EU National Regulatory Authorities (including Germany, Portugal, Spain, and the Netherlands) and the UK Medicines and Healthcare product Regulatory Authority. In the USA, the primary endpoint is the modified SARA (mSARA). This modification was based on the explicit advice of the US Food and Drug Administration, which requested the instrument be modified to:Include the domains that are the most clinically meaningful towards understanding the functional aspects of ataxia/symptoms in NPC patientsRemove domains where there is no/little movement and which may impact the interpretation and power of the tool (i.e., improve the reliability and sensitivity of the instrument)

Accordingly, the mSARA was developed as a six-item clinical rating scale consisting of the original Gait, Speech Disturbance, Finger Chase, Nose-Finger test, Fast Alternating Hand Movement, and Heel-shin slide domains. It ranges from a score of 0 to 30, where 0 is the best neurological status and 30 is the worst.

The SARA scale will be the basis for the primary efficacy estimand. The mSARA scale will be considered as a supplementary estimand. Withdrawal from study medication due to adverse events and the taking of prohibited medication will be considered as intercurrent events (ICEs) and a treatment policy strategy will be considered for these ICEs. Withdrawal or early termination from the study for unspecified reasons and lost to follow-up will not be considered as ICEs, and the subsequent data will be considered as “missing.” Should these events occur, a last observation carried forward approach will be adopted based on observations at visits 2, 3 for period 1 and visits 4, 5 for period 2.

The model for analysis will be an analysis of covariance model with the difference in the SARA scores at the end of periods I and II as the dependent variable and SARA at baseline (visit 2) as the independent variable together with an indicator variable for sequence [17]. The estimated coefficient of the indicator for sequence will provide the least squares estimate of the difference in the treatment means on division by 2. Secondary endpoints will measure other symptoms and evaluate quality of life (Spinocerebellar Ataxia Functional Index (SCAFI) [18]; Modified Disability Rating Scale (mDRS) [19, 20]; Quality of Life EQ-5D-5L for patients aged ≥ 18; EQ-5D-Y for patients aged < 18 years [21]; and Investigator, Caregiver, Patient Clinical Global Impression Scale (CGI)) [22]. Descriptive statistics will be provided for these measures at each visit, and select secondary endpoints will be evaluated statistically based on a comparison of the period differences (period II–period I) between the two treatment sequences in an analysis of covariance (ANCOVA) model with terms for baseline and treatment sequence.

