### Study design and procedures

The IB1001-301 clinical trial is a double-blind placebo-controlled crossover trial. Patients will be first assessed during a baseline period (with or without a study run-in) and randomized (1:1) to one of two treatment sequences: IB1001 followed by placebo, or vice-versa. Each treatment period will last approximately 12 weeks (84–91 days). Patients will be assessed twice during each period to allow an assessment of intra-patient variability.

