#### Randomization

At visit 2, patients will be randomized (1:1) to their respective sequence. Patients will be centrally randomized using Medpace’s ClinTrak Interactive Response Technology (IRT) web-based system. Medpace is responsible for the generation of the allocation sequence, and the IRT system will automatically assign participants to their respective sequence. The study utilizes a permuted block design for randomization. The LIVE randomization list is generated by an independent statistician based on the approved randomization plan. As the study is double-blinded, patients, their families, the study team, and the sponsor will be blinded to the randomization scheme and the sequences to which the patient is assigned. The randomization list will not be available to any person involved in the conduct of the study or the evaluation of the trial until the trial database is locked. The bioanalytical laboratory staff are authorized to receive the randomization list prior to the study conclusion to determine which samples should be analyzed according to standard operating procedures. As the trial is a crossover design, in which each patient will receive IB1001 and placebo, and serve as their own control, no stratification by age is performed.

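### The carry-forward rule lets visit 4, scored on the other treatment, stand in as the Period II outcome, which fixes the affected patient's difference at zero and dilutes the estimate

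*Protocol article*

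**What the plan says.** All places are in the protocol article.

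- **Primary efficacy endpoint, when the rule applies.** "Withdrawal or early termination from the study for unspecified reasons and lost to follow-up will not be considered as ICEs". Data after such an event count as missing. Stopping study drug because of adverse events, and taking prohibited medication, are intercurrent events under a treatment policy strategy, so the rule does not cover them.
- **Primary efficacy endpoint, the rule.** Missing scores are filled by last observation carried forward, "based on observations at visits 2, 3 for period 1 and visits 4, 5 for period 2".
- **Primary efficacy endpoint, the model.** The primary analysis is "an analysis of covariance model with the difference in the SARA scores at the end of periods I and II as the dependent variable", with visit 2 SARA and sequence as terms. The sequence coefficient divided by 2 is the treatment estimate.
- **Study design and procedures.** "Patients will be assessed twice during each period to allow an assessment of intra-patient variability".
- **Randomization.** "At visit 2, patients will be randomized (1:1) to their respective sequence".
- **Intervention periods.** Visit 6 is the last visit of the Parent Study.

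**The concern.** The visit numbering makes the first visit named for each period a score from before that period's treatment. Visit 2 is the pre-treatment baseline. Visit 4 closes Period I on the first treatment. Carrying visit 4 into Period II records an IB1001 score as a placebo outcome in one sequence, and a placebo score as an IB1001 outcome in the other. The same number then stands on both sides of the within-patient difference, so a zero is constructed and analysed as if it had been observed.

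At stake are the size of the primary estimate and the honesty of its confidence interval. Planned power is only about 80% for a 1.0-point difference, so the design has little room for a diluted estimate.

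**Working it through.** **1. What visit 4 is.** Visit 1 is baseline 1, and visit 2 is baseline 2 and randomization. With two assessments per period and visit 6 as the end, Period I holds visits 3 and 4 and Period II holds visits 5 and 6. This is inferred, because the schema figure and the supplementary schedule are not shown. The rule fits it: visits 2 and 4 are the last visits before each period's own assessments. The article describes no washout between periods and no separate Period II baseline.

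**2. The plan's power, reproduced first.** Inputs from the sample-size paragraph (at the end of Safety parameters): N = 46, so 23 per sequence; one-sided 0.05; true difference 1.0; SD 7.5 to 8.5; all correlations 0.95.

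- SD of the period difference = SD × √(2 × (1 − 0.95)). At SD 8.5 this is 8.5 × 0.3162 = 2.69.
- The sequence contrast in that difference is 2 × 1.0 = 2.0.
- Noncentrality = 2.0 / (2.69 × √(2/23)) = 2.52.
- Power at SD 8.5 is 0.81 (normal), 0.80 (noncentral t, 43 df) and 0.79 (simulated ANCOVA). At SD 8.0 and 7.5 the noncentral t gives 0.84 and 0.88.

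The stated figure of about 80% is reproduced at the upper end of the SD range.

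**3. What the rule does to the estimate.** Let D = Period II score − Period I score, τ = benefit of IB1001 (a lower score is better) and π = period effect. The mean of D is π + τ with IB1001 first and π − τ with placebo first. Half the difference is τ. Now let shares pA (IB1001 first) and pB (placebo first) be lost at random between visits 4 and 5, so that their D is 0:

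expected estimate = τ × (1 − (pA + pB)/2) + π × (pB − pA)/2

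With equal loss this reduces to τ × (1 − share lost). For τ = 1.0:

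| Lost of 46 (assumed) | Formula | Simulated, visit 4 carried | Simulated, patients left out |
|---|---|---|---|
| 1 | 45/46 = 0.98 | 0.98 | about 1.00 |
| 3 | 43/46 = 0.93 | 0.93 | about 1.00 |
| 5 | 41/46 = 0.89 | 0.89 | about 1.00 |
| 9 | 37/46 = 0.80 | 0.81 | about 1.00 |

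The simulations use SD 8.5. Coverage of the 90% interval with visit 4 carried forward is 0.89 to 0.90 up to 5 lost, and about 0.86 at 9 lost.

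**4. Power.** Visit 4 carried versus patients left out: 0.78 and 0.78 (1 lost), 0.77 and 0.76 (3 lost), 0.75 and 0.74 (5 lost), 0.69 and 0.70 (10 lost). The rule buys no power in return for its bias.

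**5. Unequal loss with a period effect.** Take 20% lost in one sequence, none in the other, π = ±0.5 (the largest period effect the article considers) and no true effect. The bias is ±0.5 × 0.2 / 2 = ±0.05 points. The simulated one-sided error is 0.036 to 0.067, against 0.048 to 0.053 when those patients are left out.

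**The case against.** **The effect is confined and, under random loss, conservative.** This largely stands. The zero arises only when visit 5 is missing as well. If visit 5 exists, an on-treatment Period II score is carried and D is not fixed. A reader might infer that the rule forces the trial's treatment contrast to zero. It does so only for each affected patient; the overall estimate would reach zero only if every patient were lost in that one window. Under equal random loss the bias is toward no effect, so it does not favour IB1001. But a known bias with under-coverage is still a poor bargain when omission avoids both.

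**The rule might be thought to inflate the type I error.** Suppose there is no true effect, SD is 8, and the 2 of 23 patients who worsen most leave the sequence that takes IB1001 second. The one-sided 5% test then rejects about 14% of the time; if they leave the sequence that takes placebo second, about 2%. The same rates appear when those patients are simply left out (14.5% and 2.2%). They come from the assumed informative dropout and are no evidence against carry-forward.

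**A patient who leaves in Period I might be thought to fall out of the analysis.** That is one reading, since visits 4 and 5 are both missing. The article does not say whether a Period I score may be carried on into Period II; if it may, that patient's D is also 0. The text settles neither reading.

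**The statistical analysis plan may deal with this.** It is not shown and may differ. But the article does more than leave the matter open: it names a rule and its visits for the primary analysis, and that rule as written is faulty.

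**Conclusion.** The point holds as a flaw in a stated rule for the primary analysis. As written, visit 4 may supply the Period II outcome although it was scored on the other treatment, and visit 2 may supply the Period I outcome although it precedes treatment. Each patient lost between visits 4 and 5 contributes a constructed zero.

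The damage is roughly proportional to the number of such patients: about 2% of the effect for 1 of 46 and about 11% for 5 of 46. At 9 of 46 it is about 20%, with coverage near 0.86. It is nil if nobody is lost there. These figures rest on the article's SD (upper end), correlation and effect size, on random loss, on assumed dropout counts and on the inferred visit structure. The documents do not support a claim of systematic bias in favour of IB1001, or of a test error caused by the rule beyond the small effect in step 5. The rule should be fixed, but it does not undermine the design.

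**What to change.** 1. State that visits 2 and 4 are never used as the outcome of the period that follows them.
2. As the minimum change, restrict carry-forward to visit 3 for Period I and visit 5 for Period II. Patients with no on-treatment score in a period then have no difference and are left out of the ANCOVA.
3. Preferably, replace carry-forward with a likelihood-based mixed model on the observed SARA scores at visits 3 to 6, with the visit 2 baseline, period, treatment and visit-within-period terms and within-patient correlation. Read the treatment contrast at week 12. This keeps the Period I scores of patients who leave later and does not treat a mid-period score as a week-12 score.
4. Add a sensitivity analysis that imputes early leavers unfavourably to IB1001. Neither carry-forward nor omission protects against outcome-related dropout, and this analysis addresses it directly.

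The cost is a wording change in the protocol and the statistical analysis plan before unblinding, and a little more analysis work. No patients, visits or data are added.

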#### Safety parameters

Adverse events (serious and non-serious), concomitant drug and non-drug therapies, safety laboratory blood samples (hemoglobin, erythrocytes, hematocrit, thrombocytes, leukocytes, sodium, potassium, urea, creatinine, serum bilirubin level, aspartate aminotransferase, alanine aminotransferase, alkaline phosphatase, lactate dehydrogenase, follicle-stimulating hormone for postmenopausal women only), and urine samples (leukocytes, nitrite, urobilinogen, protein, pH, occult blood (erythrocytes, leucocytes), specific gravity, ketones, bilirubin, glucose) will be collected routinely throughout the study. Sparse pharmacokinetic blood sampling will be conducted in the Parent Study (visit 1–visit 6). Blood samples for the quantification of N-acetyl-L-leucine in plasma will be obtained at visit 7 and visit 9. Urine samples will also be collected for measuring concentrations of N-acetyl-D-leucine at the time points designated on the schedule of events (Suppl. Tables 1 and 2). At visit 1, this urine sample serves as a key enrollment criterion testing for the use of the prohibited medication N-acetyl-DL-leucine. Vital signs, physical exams, height/weight, and electrocardiograms will also be collected at the time points designated on the schedule of events (Suppl. Tables 1 and 2). A detailed description of the safety parameters is provided in Suppl. Material I.

All statistical analyses will be detailed in a separate statistical analysis plan. For each of the primary and secondary endpoints, there will be evaluations within key subgroups: naïve versus non-naïve as determined at screening; age (pediatric versus adult at the time of enrollment); age/weight/dosing group; age of diagnosis: early-infantile (< 2 years), late-infantile (2 to < 6 years), juvenile (6 to < 15 years), adolescent/adult (≥ 15 years); disease severity based on SARA below/above the median SARA score at visit 1; gender (male versus female); region (US versus rest of world); patients taking miglustat versus patients not taking miglustat; intra-patient variability between SARA score at visit 1 (baseline 1) versus visit 2 (baseline 2) (below/above median). These evaluations will be based on plotting treatment differences together with 90% confidence intervals within each subgroup.

In a one-sided test at the *p* = 0.05 level, a total sample size of 46 in a two-treatment, two-period placebo-controlled cross-over trial achieves approximately 80% power for treatment comparisons in relation to the SARA/mSARA total score assuming a true mean difference of 1.0/0.85 (respectively) and a standard deviation for the total SARA/mSARA score between 7.5 and 8.5 and 6.375 and 7.225 (respectively) based on an analysis of covariance with the baseline SARA/mSARA score at the start of period I as the covariate. These results, based on extensive simulations, assume a correlation of 0.95 between each of the pairwise outcomes: baseline for period I, endpoint for period I, and endpoint for period II. The values for the standard deviation and the correlations used in the calculation are guided by the results of the IB1001-201 study. These levels of power are maintained when there is a positive or negative period effect of up to 0.5 and 0.425 units on the SARA/mSARA scale, respectively.

A description of data collection is provided in Suppl. Material II.

## Discussion

Given the lack of global symptomatic or disease-modifying therapies for NPC and other lysosomal diseases, there is an urgent need for effective and well-tolerated drug treatments. This multi-center, multinational randomized double- blind placebo-controlled crossover phase III trial was designed through a collaboration between national regulatory agencies, leading clinical experts, patient organizations, and the industry sponsor. This design addresses the unique ethical and practical challenges of conducting clinical trials for these orphan, heterogeneous patient populations in order to better capture N-acetyl-L-leucine’s therapeutic effect and thus expedite the development and availability of this promising drug candidate [23].

## Trial status

At the time of manuscript submission, the protocols for IB1001-301 (US V1.2 07-Jan-2022; Global: V2.0, 08-Mar-2022; Swiss V2.1 14-Jul-2022) have been accepted/approved in each country where the study will be conducted, including the US Food and Drug Administrations, UK Medicines and Healthcare products Regulatory Authority, German Federal Institute for Drugs and Medical Devices, Slovakia Štátny ústav pre kontrolu liečiv, Switzerland Swissmedic, Netherlands Central Committee on Research Involving Human Subjects, Czech Republic State Institute for Drug Control, and Australia Therapeutic Goods Administration as well as respective research ethics committees (REC)/institutional review boards (IRB) (active approved protocol version varies based on status of enrollment per site/per study). The first study participant was enrolled on 30 June 2022. Recruitment is ongoing and expected to complete December 2022.

## Data Availability

All investigators will be provided with full access to all the final data set in the study. Data sharing is not applicable to this article as no datasets were generated or analyzed during the current studies (study protocols).

## Abbreviations

ANCOVA: Analysis of covariance
CGI: Clinical Global Impression
DSMB: Data safety monitoring board
EP: Extension Phase
GM2: GM2 gangliosidoses
ICE: Intercurrent events
IRB: Institutional review boards
IRT: Interactive Response Technology
mDRS: Modified Disability Rating Scale
mSARA: Modified Scale for the Assessment and Rating of Ataxia
NPC: Niemann-Pick type C
NPC-CSS: NPC clinical severity scale
PI: Principal investigator
REC: Research ethics committees
SARA: Scale for the Assessment and Rating of Ataxia
SCAFI: Spinocerebellar Ataxia Functional Index
